## STATISTICAL PLAN AND CONSIDERATIONS

**Sample Size Determination** To detect a mean difference in  $\Delta$ -creatinine of  $\geq 0.35$  mg/dL at conventional two-sided (type I error)  $\alpha = 0.05$  and power of 80% requires measurements on 65 patients per treatment group (130 total). **This** sample size of 65 patients per group does not provide adequate power around the secondary endpoint to detect a decrease in the development of stage 2 AKI. At this size we have 80% power to detect a 70.9% reduction the development of Stage 2 AKI. At a cutoff of greater than 0.01 over 30% of all patients enrolled are at risk for developing Stage 2 AKI. Thus by enrolling 90 patients per arm we are able to ensure that we achieve 80% power for the primary and have 80% power to detect a 60% reduction in the development of Stage 2 AKI. Should every patient enrolled stay in the study we will have even more power approaching 90% power for the primary endpoint.

**Statistical Considerations:** *Randomization* Patients will be randomized 1:1 to two arms (standard of care (SOC) vs. ENC using an ESTOP-AKI stratified REDCAP-based algorithm. Assignments will be made within strata of ESTOP-AKI risk scores ( $>0.01$  to 0.569 and  $\geq 0.57$  to protect against imbalances in randomization on key factors (age, race, baseline SCr, severity of illness, patient location ). To balance the number assigned per arm, permuted assignment blocks of variable size that are unknown to investigators will be used.

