**Analytic Methods - Primary endpoint:** Difference of mean  $\Delta$ -SCr between the ENC and SOC group. Randomized assignment stratified by predicted risk (ESTOP-AKI score) maximizes the potential for equal distribution of potential confounding factors by treatment group. Primary analysis is thus a comparison of means from a 2-factor (treatment and stratification level) ANOVA model. If there is evidence of imbalance in key factors (baseline SCr, age, sex, hospital service type), then a secondary analysis using linear model methods will be conducted to compare adjusted means. For patients who die within 7-days or receive RRT we will analyze the data with  $\Delta$ -SCr set at their maximum SCr prior these events. **Secondary endpoints:** For binary outcomes (i.e., AKI stage, ICU transfer), proportions will be compared between ENC and SOC groups via the binomial test. The primary analysis will be a direct comparison of these proportions. Logistic regression analysis may be conducted to account for covariate imbalances. Time to discharge (LOS) and time to peak SCr distributions will be compared by group using nonparametric statistics for differences in specific

quantiles (e.g. medians) and other summaries (means). These endpoints can also be approached from a survival analysis modeling perspective, with treatment and other covariates investigated in relation to event rates.

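### The test named for the binary secondary endpoints is strictly a one-sample test, and their primary comparison omits the ESTOP-AKI randomisation stratum; a stratified two-sample test should be named

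*Protocol*

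**What the plan says.** All references are to the Protocol, Statistical Plan and Considerations.

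- **Binary secondary endpoints (Analytic Methods).** AKI stage and ICU transfer are the outcomes mentioned, and "proportions will be compared between ENC and SOC groups via the binomial test". The text continues: "The primary analysis will be a direct comparison of these proportions". The stratum is not mentioned.
- **Adjustment of these endpoints.** "Logistic regression analysis may be conducted to account for covariate imbalances". This is optional and does not name the stratum.
- **Primary endpoint (same section).** "Primary analysis is thus a comparison of means from a 2-factor (treatment and stratification level) ANOVA model". Here the stratum is part of the analysis.
- **Randomisation (Statistical Considerations).** "Patients will be randomized 1:1 to two arms", and "Assignments will be made within strata of ESTOP-AKI risk scores". There are two strata, split at a score of 0.57.
- **Planning figure (Sample Size Determination).** With 90 patients per arm the trial is said to have 80% power for a 60% reduction in Stage 2 AKI, from a rate put at somewhat more than 30%.

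**The concern.** There are two faults in the same short piece of text.

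First, the name of the test is wrong for the job. In standard usage a binomial test sets one observed proportion against a fixed value. Here both arms are random samples, so a test of two independent proportions is needed.

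Second, even with the name corrected, the comparison leaves out the factor on which patients were randomised. Stratified randomisation balances the arms on ESTOP-AKI risk, which lowers the true variance of the difference in proportions whenever the stratum predicts the outcome. The Background reports an AUC of 0.83 for stage 3 AKI for this score, so the stratum should predict Stage 2 AKI to some degree. An unstratified test uses a standard error that ignores this balance. The interval is then wider than it need be and the test rejects less often than its nominal 5%.

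What is at stake is some efficiency on the binary secondary endpoints. One of these, Stage 2 AKI, is the Protocol's stated reason for enrolling 90 rather than 65 per arm.

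**Working it through.** **Step 1. Which test did the planning assume?** Inputs from Sample Size Determination: control rate 30%, 60% reduction (so 12%) and 80% power. The two-sided 0.05 level is stated for the primary endpoint and assumed to carry over. For two independent proportions with p1 = 0.30, p2 = 0.12, difference d = 0.18 and mean 0.21:

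- m = [1.960 × √(2 × 0.21 × 0.79) + 0.842 × √(0.30 × 0.70 + 0.12 × 0.88)]² / 0.18² = (1.129 + 0.473)² / 0.0324 ≈ 79.2, so 80 per arm.
- With continuity correction: (m/4) × [1 + √(1 + 4/(m × d))]² = 19.80 × (1 + √1.281)² ≈ 89.96, so **90 per arm, as stated**.

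The Protocol's other figure (70.9% reduction, 65 per arm) gives 63 by the same route, within two patients. The planning is therefore that of a two-sample test.

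**Step 2. What does leaving out the stratum do to the type I error?** Let w be the share of patients in the high stratum, pH and pL the event rates in the two strata, and p the overall rate, held at 0.30. The Protocol gives none of w, pH or pL, so they are assumed. With assignment balanced within strata, the ratio of the true variance to the variance that the unstratified test uses is

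V = [w × pH(1 − pH) + (1 − w) × pL(1 − pL)] / [p(1 − p)],

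and the true two-sided type I error is 2 × [1 − Φ(1.96/√V)].

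- Weak case, w = 0.10, pH = 0.50: pL = (0.30 − 0.05)/0.90 = 0.278. V = (0.0250 + 0.1806)/0.21 = 0.979. Type I error 4.8%.
- Strong case, w = 0.30, pH = 0.80: pL = (0.30 − 0.24)/0.70 = 0.086. V = (0.0480 + 0.0549)/0.21 = 0.490. Type I error 0.5%.

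**Step 3. What does a stratified test give at the same size?** Simulation with 90 per arm and 400,000 trials per setting, under no effect and under a common risk ratio of 0.4 (30% versus 12% overall):

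| w | pH | pL | Type I, unstratified | Type I, CMH | Power, unstratified | Power, CMH |
|---|---|---|---|---|---|---|
| 0.10 | 0.50 | 0.278 | 4.7% | 5.0% | 85.5% | 85.9% |
| 0.20 | 0.60 | 0.225 | 3.8% | 5.0% | 86.5% | 88.2% |
| 0.20 | 0.80 | 0.175 | 1.9% | 4.9% | 88.1% | 92.4% |
| 0.30 | 0.80 | 0.086 | 0.5% | 5.0% | 90.5% | 96.3% |
| 0.50 | 0.55 | 0.050 | 1.9% | 4.9% | 88.2% | 92.0% |

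The simulated type I errors agree with the formula in Step 2. The power gain runs from about 0.4 points (first row) to about 6 points (fourth row). When both strata have a 30% event rate, the two tests have practically the same power, about 85.5% each. The stratified test lost power in no scenario run.

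**The case against.** The strongest reply is that this is loose naming and nothing more. The sentence speaks of a comparison between two groups, the next calls it a direct comparison of proportions, no fixed reference proportion appears anywhere, and the planning figures are two-sample. That stands, and it disposes of the stronger reading.

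A reader might infer from the test's name that the false-positive rate for these endpoints is 15% to 17%. The arithmetic is right for a literal one-sample test that treats the observed SOC proportion as known. Asymptotically the error is 2 × [1 − Φ(1.96/√2)] = 16.6%, and exact enumeration at 90 per arm and a 30% rate gives 16.1%. But the Protocol does not describe that procedure, so the figure is not a consequence of the plan.

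It can also be said that an unstratified two-sample test is valid, that the Protocol nowhere promises to stratify every analysis, and that the size of the gain rests on assumed stratum splits and rates. All of this stands, and it limits the point to one of efficiency and consistency.

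The optional logistic regression is sometimes read as letting the main result move with a look at the data. It does not, because the direct comparison is named in advance as primary. An exact version for sparse outcomes such as RRT, and the covariates of any supportive model, belong in a statistical analysis plan and are not claimed as gaps here.

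What remains is that the Protocol does fix a test and a primary comparison for these endpoints. The test is misnamed, and the comparison drops the stratum that the same section uses for the primary endpoint.

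**Conclusion.** The point holds as a minor one. The named test should be corrected on any reading. On the likely reading, an unstratified two-sample comparison, the analysis is valid but conservative. Under the assumptions shown (10% to 50% of patients in the high stratum, event rates of 50% to 80% there, 30% overall), its true type I error is about 0.5% to 4.8%, and a stratified test gains about 0.4 to 6 points of power at 90 per arm. The upper end needs a strongly prognostic stratum; with no prognostic value the gain is nil.

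The primary endpoint is unaffected. So is the stated 80% power for Stage 2 AKI, which the unstratified test already meets: 84.9% without continuity correction and 81.2% by Fisher's exact test, for 30% versus 12% at 90 per arm.

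**What to change.** In Analytic Methods, Secondary endpoints, replace the named test and the sentence on the direct comparison with wording such as: *Binary secondary endpoints will be compared between ENC and SOC by a two-sided Cochran-Mantel-Haenszel test stratified by the ESTOP-AKI randomisation stratum, with the Mantel-Haenszel risk difference and its 95% confidence interval. This stratified comparison is the primary analysis of these endpoints.*

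This brings the binary endpoints into line with the primary-endpoint model and with the randomisation. It costs one sentence, with no further patients or data, since the stratum is recorded at randomisation. It should be made before outcomes are compared by arm.

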## **RISKS AND BENEFITS**

**Risks** The only risk to subjects is minimal risk associated with blood draw which include bruising and irritation at the sight of penetration. Also subjects are at minimal risk for loss of confidentiality.

**Benefits to subject:** There may or may not be direct medical benefit to those subjects included in the intervention group.

**Interim Monitoring** – An independent Data and Safety Monitoring Board (DSMB) and its membership has been established for this trial. Study conduct and progress will be reviewed on multiple occasions with a mandatory analysis once 20-25% enrollment (~ 20 per arm) for safety and feasibility as well as a futility / efficacy analysis at 50% enrollment (~40 per arm).

